### **Serious Adverse Events (SAEs)**

A Serious Adverse Event (SAE) is defined by the International Conference on Harmonization (ICH) guidelines and GCP guidelines as any AE fulfilling at least one of the following criteria:

- Results in deaths.
- Life-threatening – defined as an event in which the subject was, in the judgment of the Investigator, at risk of death at the time of the event;
- Requiring subject's hospitalization or prolongation of existing hospitalization
- Resulting in persistent or significant disability or incapacity (i.e., a substantial disruption of a person's ability to conduct normal life functions).
- Congenital anomaly or birth defect.
- Is medically significant or requires intervention to prevent at least one of the outcomes listed above

Life-threatening refers to an event in which the subject was at risk of death at the time of the event. It does not refer to an event that hypothetically might have caused death if it were more severe.

Important medical events that may not immediately result in death, be life-threatening, or require hospitalization may be considered as SAEs (optional!) when, based upon appropriate medical judgment, they may jeopardize the subject and may require medical or surgical intervention to prevent one of the outcomes listed in the definitions above. This means an individual case decision.

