## 8. Potential Risks

Metyrapone is a selective inhibitor of the 11-b hydroxylase and is frequently used in the medical treatment of Cushing's syndrome because of its rapid effects (9).

Being generally well tolerated minor, but common side effects include **gastrointestinal side effects** including diarrhea, nausea and vomiting, as well as **fatigue, dizziness and headache**, which are all rapidly reversible after interruption of the drug.

Furthermore, side effects of **hyperandrogenemia** can occur in women, resulting rarely in hirsutism and alopecia. Hyperandrogenemia spontaneously resolves after interruption of metyrapone.

It is important to note that these side effects appear to be largely depending on the daily dose of metyrapone, as well as on the severity of hypercortisolism before treatment of Cushing's syndrome. We therefore assume, that the risk of these side effects is limited in our study, using small daily doses of metyrapone (750 mg per day) in patients with only mild hypercortisolism.

The most dangerous side effect of metyrapone is **adrenal insufficiency**, which can lead to life threatening adrenal crisis in situations of acute stress. Metyrapone is a short-acting steroidogenesis inhibitor and doses given at 6 p.m. and 10 p.m. were shown to lower only cortisol levels in the evening and during the night, without affecting cortisol levels in the morning and afternoon (10). We therefore assume that the risk of adrenal insufficiency is very limited with our treatment regime. However, all study participants will be educated on earliest clinical signs and symptoms of adrenal insufficiency. They will be systematically instructed in the supplementation of Hydrocortisone by tablets in case of the suspicion of an adrenal insufficiency and by subcutaneous injection of hydrocortisone in case of the suspicion of an adrenal crisis. In addition, clinical signs and symptoms of adrenal insufficiency will be assessed systematically at every study visit.

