### **Hospitalization – Prolongation of existing hospitalization**

Hospitalization is defined as an overnight stay in a hospital unit and/or emergency room. An additional overnight stay defines a prolongation of existing hospitalization.

The following is not considered an SAE and should be reported as an AE only:

- Treatment on an emergency or outsubject basis for an event not fulfilling the definition of seriousness given above and not resulting in hospitalization.

The following reasons for hospitalizations are not considered AEs, and therefore not SAEs:

- Hospitalizations for cosmetic elective surgery, social and/or convenience reasons.
- Elective treatment of a pre-existing disease or medical condition that did not worsen, e.g., hospitalization for chemotherapy for cancer, elective hip replacement for arthritis.

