#### ***Severe***

Event may cause noticeable discomfort; usually interferes with daily activities; subject may not be able to continue in the study; the AE produces sequelae, which require prolonged therapeutic intervention.

A mild, moderate or severe AE may or may not be serious. These terms are used to describe the intensity of a specific event (as in mild, moderate, or severe myocardial infarction). However, a severe event may be of relatively minor medical significance (such as severe headache) and is not necessarily serious. For example, nausea lasting several hours may be rated as severe, but may not be clinically serious. Fever of 39°C that is not considered severe may become serious if it prolongs hospital discharge by a day. Seriousness rather than severity serves as a guide for defining regulatory reporting obligations.

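### The protocol makes one seriousness criterion both binding and optional, so a suspected adrenal crisis treated without an overnight stay may be left non-serious; separately, the severity grades contradict their own examples

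*Protocol*

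**What the plan says.** **Seriousness.** In Section 9 of the protocol, under Serious Adverse Events (SAEs), an SAE is "any AE fulfilling at least one of the following criteria". Six criteria follow. The sixth reads "Is medically significant or requires intervention to prevent at least one of the outcomes listed above". The closing paragraph of the same subsection returns to important medical events that could endanger the subject and could need intervention to avert a listed outcome. It says that these "may be considered as SAEs (optional!) when, based upon appropriate medical judgment" and adds "This means an individual case decision".

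The life-threatening criterion is confined to actual risk of death at the time, in the investigator's judgment. The next subsection says "Hospitalization is defined as an overnight stay in a hospital unit and/or emergency room". It leaves emergency or outpatient treatment as an ordinary adverse event when the seriousness definition is not met.

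**Severity.** The moderate grade is described as leaving no sequelae. For the severe grade, "the AE produces sequelae, which require prolonged therapeutic intervention". The explanatory text under the same grade then mentions a severe headache and says that "nausea lasting several hours may be rated as severe, but may not be clinically serious".

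**The risk concerned.** Section 8 (Potential Risks) treats adrenal insufficiency, with possible adrenal crisis, as the gravest harm of the drug. Participants are taught to act "by subcutaneous injection of hydrocortisone in case of the suspicion of an adrenal crisis".

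**The concern.** Medical judgment about whether an event is medically significant is normal and is not the problem. Here the option attaches to the SAE label itself. Even after the investigator has judged that an event could endanger the subject and could need intervention, the closing paragraph says only that it may be called serious. Two investigators with the same facts and the same medical opinion could classify it differently, and both could cite the protocol.

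The harm that Section 8 puts first can fall into this gap. Participants are instructed in early treatment of a suspected crisis, so an event may resolve before it meets the death, hospitalization or disability criteria. If it is then left non-serious, the report to the ethics committee and the authority under Reporting procedures for SAEs is not triggered.

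The severity conflict is a lesser matter. Nausea and headache are listed in Section 8 as common effects of metyrapone, so graders will meet the contradiction in routine use.

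**Working it through.** There is no figure in the plan to reproduce; the check consists of applying the rules to one event.

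**Event:** a suspected adrenal crisis, treated by hydrocortisone injection, resolved without an overnight stay and without sequelae. This is a constructed example; the documents report no such case.

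| Criterion (Section 9) | Met? |
|---|---|
| Death | No |
| Life-threatening | Investigator's judgment; can be answered no if the injection averted the risk, because hypothetical danger is excluded |
| Hospitalization | No, since no overnight stay |
| Disability or incapacity | No |
| Congenital anomaly | No |
| Medically significant, or intervention needed to prevent a listed outcome | Can be met under the list; optional under the closing paragraph |

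If the investigator answers no on life-threatening and declines the option on the sixth criterion, the event is an ordinary adverse event. If either is answered yes, it is an SAE. Both routes are open in the text.

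**Severity of the same event.** By the literal definitions, no sequelae and no prolonged intervention point to moderate. By the examples under the severe grade, severe is available: several hours of nausea or a headache would not ordinarily leave sequelae, and none are mentioned. Definition and examples cannot both hold.

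**Scale.** Input: n = 15 treated patients (Working plan B; Sample size calculation). Exact (Clopper-Pearson) 95% limits:

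- 0/15: lower limit 0; upper limit 1 − 0.025^(1/15) = 0.218, so 0% to 21.8%.
- 1/15 = 6.7%: lower limit 1 − 0.975^(1/15) = 0.0017; the upper limit solves (1 − p)^15 + 15p(1 − p)^14 = 0.025, giving p = 0.319. So 0.2% to 31.9%.

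The documents give no event rate. As an assumption, take a per-patient risk p over 12 weeks; the chance of at least one event among 15 is 1 − (1 − p)^15:

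- p = 2%: 26%
- p = 5%: 54%
- p = 10%: 79%

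These figures show only how much one classification weighs in a group of 15. They are not evidence for the contradiction, which rests on the text.

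**The case against.** The strongest reply is that the two clauses are not identical. The listed criterion covers an event that does require intervention; the closing paragraph covers events that might. Where an injection was truly needed to prevent a listed outcome, the listed criterion applies, and a genuine crisis can also be life-threatening, as Section 8 itself describes it. Where the suspicion was mistaken, non-serious may be the correct classification. The rule on emergency treatment does not downgrade anything by itself, since it refers back to the seriousness definition. And judgment on medical significance remains whatever the wording.

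Much of this stands. It shows that misfiling is permitted and not forced, and that not every suspected crisis should be an SAE. It does not remove the conflict: medical significance appears in the binding list without qualification, and the closing paragraph makes important medical events optional even after judgment has been exercised.

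A reader might also infer more than the documents support:

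- *That most adrenal crises would be serious only through the optional route.* No event rate or distribution of outcomes is given.
- *That nobody but the sponsor-investigator looks at the classification.* Under Periodic Monitoring, a monitor with no other study role has access to source documents and verifies SAE documentation. The monitor can raise a query, though against the same contradictory rule.
- *That the stopping provision turns on these classifications.* Premature termination of the study rests on an overall risk-benefit judgment, not on an SAE count, and signs of adrenal insufficiency are assessed at every visit.
- *That the event would be lost.* It would still be recorded as an adverse event.
- *That the severity conflict affects regulatory reporting.* The text under the severe grade ties reporting to seriousness, not severity. Nor is a severe grade strictly unavailable for events without sequelae, because the examples allow it.

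**Conclusion.** Both contradictions are in the current text and should be reconciled.

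The seriousness conflict matters more. A suspected adrenal crisis treated by injection and resolved without an overnight stay may be left as a non-serious adverse event, with no SAE report, provided that the investigator does not judge it life-threatening and does not take up the option. That conclusion needs only the wording of Sections 8 and 9 and this one scenario. It makes no claim about how often the scenario would occur. With 15 treated patients, a single such decision determines whether the SAE count is zero or one.

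The severity conflict is a separate and smaller defect, confined to grading in the CRF and to tolerability summaries.

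**What to change.** 1. Under Serious Adverse Events (SAEs), delete the optional marker and reword the closing paragraph so that an event judged to meet the sixth criterion is an SAE. Limit the case-by-case decision to whether the criterion is met.
2. State that suspected adrenal crises and uses of the hydrocortisone injection are assessed for seriousness under that criterion, with the assessment recorded. This should not make each one automatically an SAE.
3. Remove sequelae from the moderate and severe grades so that they agree with the examples given. No information is lost, because the outcome field under Reporting procedures already has a category for resolution with sequelae.

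These are reporting definitions; no dose or treatment rule changes. The cost is protocol and CRF wording, and possibly a few more SAE reports.

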### **Hospitalization – Prolongation of existing hospitalization**

Hospitalization is defined as an overnight stay in a hospital unit and/or emergency room. An additional overnight stay defines a prolongation of existing hospitalization.

The following is not considered an SAE and should be reported as an AE only:

- Treatment on an emergency or outsubject basis for an event not fulfilling the definition of seriousness given above and not resulting in hospitalization.

The following reasons for hospitalizations are not considered AEs, and therefore not SAEs:

- Hospitalizations for cosmetic elective surgery, social and/or convenience reasons.
- Elective treatment of a pre-existing disease or medical condition that did not worsen, e.g., hospitalization for chemotherapy for cancer, elective hip replacement for arthritis.

### **SAEs related to investigational drug**

Such SAEs are defined as SAEs that appear to have a reasonable possibility of causal relationship (i.e., a relationship cannot be ruled out).

### **Suspected unexpected serious adverse reactions (SUSARs)**

SUSARs are all serious adverse reactions with **suspected** (not only possible) causal relationship to the study drug that is unexpected (not previously described in the Summary of Product Characteristics or Investigator's brochure) and serious.

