## **7. Study medication**

Active agent and characteristics: Metyrapone

Trade name of the agent: Metycor 250 mg

Supply Chain: Metycor will be provided by HRA pharma. The drug will be stored in accordance with the prescribing information.

IMP administration and handling: Metycor will be taken orally with a dose of 500 mg at 6 p.m. and 250 mg at 10 p.m.

Drug Accountability and assessment of subjects' compliance: Drug accountability and subjects' compliance will be directly observed by the investigators. Additionally, batch numbers will be recorded in the CRF.

Concomitant medication: Concomitant medication will be registered at every study visit.

Randomization and blinding: This study is designed as an open label, single armed trial. No randomization and blinding will be performed.

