#### ***Possibly***

- The AE has a reasonable temporal relationship with drug administration.
- The AE may equally be explained by the study subject's Clinically state, environmental or toxic factors, or concomitant therapy administered to the study subject.
- The relationship between study drug and AE may also be pharmacologically or clinically plausible.

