**Reporting procedures**

A special section is designated to adverse events in the case report form. The following details must thereby be entered:

- Type of adverse event
- Start (date and time)
- End (date and time)
- Severity (mild, moderate, severe)
- Serious (no / yes)
- Unexpected (no / yes)
- Outcome (resolved, resolving, not resolved, resolved with sequelae, unknown, fatal)
- Relation to study drug (Related/ Probably/ Possibly/ Unlikely/ Not related/ Not assessable)

Adverse events are to be documented in the case report form in accordance with the above-mentioned criteria.

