**Reporting procedures for SAEs**

In case of a serious adverse event, the Investigator has to use all supportive measures for best patient treatment. A written report is also to be prepared and should at least contain the following:

- Patient number
- Patient: sex
- The suspected investigational medical product (IMP)
- The adverse event assessed as serious
- Short description of the event and outcome

If applicable, the initial report should be followed by the Follow up report, indicating the outcome of the SAE. The reports will be submitted to the local ethics-committee, the local authorities (BASG) and to Astra Zeneca (the supplier of the study drug).

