### **Reporting procedures for SUSARs**

It must be remembered that the regulatory authorities, and in case of SUSARs which could possibly concern the safety of the study participants, also the Institutional Review Board / Independent Ethics Committee (IRB / IEC) are to be informed. Such reports shall be made by the study management and the following details should be at least available:

- Patient number
- Patient: age in years, sex
- Name of Investigator and investigating site
- Period of administration
- The suspected investigational medical product (IMP)
- The adverse event assessed as serious and unexpected, and for which there is a suspected causal relationship to the IMP
- Concomitant disease and medication
- Short description of the event:
  - Description
  - Onset and if applicable, end
  - Therapeutic intervention
  - Causal relationship
  - Seriousness criteria or reportable reason

Electronic reporting should be the expected method for reporting of SUSARs to the competent authority. In that case, the format and content as defined by the ICH E2A

Guideline should be adhered to. The latest version of MedDRA should be applied. Lower level terms (LLT) should be used.

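### Section 9 sets two different causality thresholds for related serious events and SUSARs, and sends SAE reports to a company that the rest of the protocol does not name as supplier

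*Protocol*

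**What the plan says.** All the causality and seriousness rules are in section 9 of the protocol.

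- **Related SAEs** (SAEs related to investigational drug) are "SAEs that appear to have a reasonable possibility of causal relationship (i.e., a relationship cannot be ruled out".
- **SUSARs** (Suspected unexpected serious adverse reactions) are serious adverse reactions whose relationship to the drug is suspected, "not only possible) causal relationship to the study drug that is unexpected".
- **The grade Possibly** (Relationship to study drug) requires a reasonable temporal relationship, allows that other causes may explain the event equally well, and adds: "The relationship between study drug and AE may also be pharmacologically or clinically plausible".
- **The CRF field** (Reporting procedures) offers six grades: "Relation to study drug (Related/ Probably/ Possibly/ Unlikely/ Not related/ Not assessable".
- **The SUSAR report** (Reporting procedures for SUSARs) covers an event "for which there is a suspected causal relationship to the IMP".
- **SAE reports** (Reporting procedures for SAEs) go to the local ethics committee, "the local authorities (BASG) and to Astra Zeneca (the supplier of the study drug".
- **The supplier** in section 7, Study medication, is different: "Metycor will be provided by HRA pharma". The product table at the front of the protocol also gives HRA Pharma.
- **Seriousness** (Serious Adverse Events) is met by any one of a list of criteria, one of which is medical significance. Later in the same section, important medical events "may be considered as SAEs (optional!) when, based upon appropriate medical judgment".

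**The concern.** These are working rules that site staff apply event by event. The definitions of a related SAE and of a SUSAR stand next to each other and use different causality tests. A SUSAR is described as a kind of serious adverse reaction, so one would expect unexpectedness alone to separate it from other drug-related SAEs. Here a second, stricter causality test is added, and its key word, suspected, is defined only by what it leaves out.

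At stake is how a serious, unexpected event with an uncertain drug cause is classified, and how much detail is reported about it. Working plan B gives metyrapone to 15 patients (plus any replacements) for 12 weeks, so with few treated patients the handling of a single event matters.

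The supplier conflict decides whether the company that provides the drug is told of SAEs under this protocol. The optional wording leaves it unclear whether an important event managed without a hospital stay must be classed as serious.

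**Working it through.** No figure is involved, so the check sets the texts side by side.

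**1. Causality.** Each CRF grade is read against the two definitions, using the descriptions under Relationship to study drug.

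| Grade | Drug-related SAE (relationship not excluded) | SUSAR (suspected, more than possible) |
|---|---|---|
| Related | meets it | meets it |
| Probably | meets it | meets it on a natural reading |
| Possibly | meets it: timing fits and a drug cause may be plausible | excluded by the bracketed words |
| Unlikely | open: timing fits, but another explanation is plausible | does not reach it |
| Not related | does not meet it | does not meet it |
| Not assessable | open: causality cannot be judged | not stated |

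The two rules give opposite answers for *Possibly*. For *Unlikely* and *Not assessable*, the related-SAE test itself gives no clear answer, because neither grade plainly excludes a relationship. Neither the CRF list nor the SUSAR reporting section resolves this: the first lists the grades without saying which count as related or suspected, and the second repeats the word suspected without defining it.

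**2. What a *Possibly* event loses.** The SAE reporting section applies no causality filter, so the event still goes to the ethics committee and the BASG. The minimum SAE report holds patient number, sex, product, event, and a short description with outcome. The SUSAR report adds age, investigator and site, period of administration, concomitant disease and medication, onset and end, therapeutic intervention, causal relationship and the seriousness criterion. It also expects electronic submission in a standard format with MedDRA coding. The loss is therefore the classification, this added content and the electronic route.

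**3. Recipient.** Two places (the front product table and section 7) link the drug to HRA Pharma. One place (Reporting procedures for SAEs) calls Astra Zeneca the supplier and makes it a recipient. The protocol gives Astra Zeneca no other role, and HRA Pharma is not on the recipient list.

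**4. Seriousness.** The list requires at least one criterion and includes medical significance, or the need for intervention to prevent a listed outcome. The later paragraph covers nearly the same events, those that may need intervention to prevent such outcomes, but makes their classification optional and a decision for the individual case. The hospitalization section allows AE-only reporting of emergency or outpatient treatment only where the seriousness definition is not met. That sends the reader back to the definition that contains the ambiguity.

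**The case against.** The strongest defence is that a related SAE and a SUSAR are different things, and a narrower subset is not in itself a contradiction. That is formally right. However, the subset is narrowed by a second causality test as well as by unexpectedness, and suspected is never tied to the CRF grades, so the conflict over *Possibly* remains.

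Several objections limit the consequences, and they stand:

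- A reader might infer that *Possibly* events are lost to expedited reporting. The protocol sets no expedited timeline for SAEs or SUSARs, and the events still reach the ethics committee and the BASG.
- A reader might infer that SAE counts would be understated because of the SUSAR definition or the wrong recipient. Seriousness and causality are separate CRF entries, and AEs are recorded whatever their relationship to the drug. Neither rule can change the SAE count.
- A reader might infer that every report meant for the supplier would go astray. That assumes staff would follow the wrong name literally. The name looks like a carry-over from another protocol (an inference), and a separate arrangement with HRA Pharma may exist that is not shown.
- On seriousness, the criterion list and the hospitalization section both point towards classing a medically significant event as an SAE, and judgement on important medical events is a fair principle. What remains is an ambiguity in wording, not a rule that allows such events to be downgraded.

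**Conclusion.** Two contradictions in the operative text hold. First, the causality threshold for SUSARs is stricter than that for drug-related SAEs, so a serious, unexpected event graded *Possibly* is related but not a SUSAR. Second, the SAE recipient named as supplier is not the supplier named in two other places. The optional wording for important medical events is a third, lesser inconsistency.

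The extent is one grade of six in direct conflict, two more not mapped, and one wrong name. The causality point rests on reading the bracketed words as excluding the CRF grade *Possibly*, which is their plain sense. The supplier point rests on the front table and section 7 being right; they agree with each other.

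The matter concerns the classification and routing of safety reports in working plan B. The documents do not support extending it to missing SAEs, missed deadlines or any effect on the primary outcome, sample size, alpha or efficacy analysis.

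**What to change.** Make these changes in one amendment to section 9:

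1. Use one causality threshold. Delete the bracketed qualifier after the word suspected in the SUSAR definition, so that it agrees with the definition of related SAEs.
2. Map all six CRF grades to that threshold in writing. *Possibly*, *Probably* and *Related* meet it. The sponsor should state explicitly how *Unlikely* and *Not assessable* are treated, because the criterion alone does not settle them.
3. In the SAE reporting section, replace the company name with the supplier given in the front table and section 7.
4. Remove the bracketed word optional from the paragraph on important medical events, so that it agrees with the criterion list above it.

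The cost is a few wording changes and possibly a few more SUSAR reports. No assessment, visit or analysis changes.
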